### Eligibility criteria {10}

The following are the inclusion criteria:Aim 1: Clinicians (physicians, nurse practitioners, physician assistants), nurses, CPs, administrators, case managers, social workers, and other stakeholders likely to be engaged in or impacted by the CACP programAim 2: Adults (age ≥ 18 years) who are (1) currently admitted to the ED or hospital or (2) in a pre-hospital (i.e., outpatient) setting but being considered for referral to the ED or hospital and who do not require hospital-level monitoring or care other than services that could be delivered by CPs in the ambulatory setting if such services were available to themAim 3: Patients enrolled in the CACP program, CPs affiliated with the CACP program, health care team members (clinicians, case managers, social workers) who referred participants enrolled in the CACP intervention arm, and administrators involved with the CACP program or affiliated programs and services

The following are the exclusion criteria:Aim 1: No exclusion criteria.Aim 2: Patients will be excluded if (1) the referring clinician believes they require ED or hospital care; (2) they or their legal guardian/representative are unable or unwilling to give written informed consent; (3) they demonstrate clinical, behavioral, or cognitive instability, as determined by the referring clinician or the CACP service; (4) their living conditions are deemed unsafe for CPs to enter (e.g., the patient refuses to secure weapons or animals prior to CP arrival); (5) they were enrolled in the trial during an earlier hospitalization or ED visit; or (6) they are requesting services in a location outside the CACP service area or in a skilled nursing facility (SNF). The referring service completes a checklist prior to referring patients to the CACP program (available as a system smart phrase within the EHR) that explains these criteria, including patient confirmation of factors related to the safety of CPs conducting home visits. Patients can only be enrolled in the trial if the CACP program has the census capacity to accept new patients.Aim 3: There are no exclusion criteria for clinicians or other clinical or administrative stakeholders. Patient participants will be excluded from recruitment to interviews if they (1) have a communication barrier due to medical illness or cognitive impairment or (2) are seriously ill or hospitalized at the time of interview recruitment.

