#### Intervention description {11a}

The CACP program is an extension of an established care delivery model offered by the Mayo Clinic Ambulance Service. In the CACP program, the referring clinician identifies services or interventions clinically required for the patient. This may include patient education, clinical reassessment, laboratory specimen collection, medication administration, wound care, and other services within the CP scope of service. Visits are limited to up to two per day and are generally no more than 2 h in duration. The referring service or the patient’s primary care provider (PCP) or another ambulatory care provider, as appropriate, oversees clinical care with the support of the CP medical director. CPs will communicate with the referring service and/or their medical director as appropriate (usually after every visit but individualized based on the patient’s need and instructions provided by the referring service) via EHR inbox messages, the EHR chat function, or telephone. Patients will graduate from the program once the goals outlined in the referral are completed. Upon graduation, the CP team will communicate directly with a clinician assuming the patient’s care (e.g., PCP).

The CACP program will be available to patients at no cost, and services provided by CPs under this trial will not be submitted to participating patients’ insurance. If CPs facilitate or assist with a service performed by other members of the health care system, the services performed by others will be processed by the patient’s insurance as per usual procedures. For example, if a patient is seen for clinical assessment, venipuncture with laboratory sample collection, and administration of intravenous fluids, the assessment, venipuncture, IV start, and IV fluids themselves will be free to the patient. However, the analysis of the blood sample conducted by a clinical laboratory after it is collected and delivered by CPs will be processed through insurance. In contrast, point-of-care testing performed by CPs will be at no cost to the patient.

Participants randomized to usual care will be treated without consideration of CP care options. We anticipate that most will be referred to the ED and admitted to the hospital or have alternative care pathways (e.g., home health agency, SNF, frequent clinic visits) to meet their clinical needs. The start time for both cohorts will be the day after randomization.

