### Outcomes {12}

Trial outcomes for the three specific aims are detailed in Tables 1 and 2. Aim 1 is a formative evaluation of the implementation context that seeks to rapidly identify and address anticipated barriers and challenges, as well as identify opportunities that could impact the successful implementation of the pragmatic trial and the CACP program. It involves qualitative interviews with CPs, clinicians and other members of the health care team, and administrators, in the 3-month period directly before trial enrollment commences with anticipated qualitative outcomes related to acceptability and feasibility, as well as detailed recommendations for targeted actions.

**Table 1 Tab1:** Elements of primary and secondary outcomes

Domain	Specific measurement	Specific metric	Method of aggregation	Time point
Potential barriers to CACP implementation (aim 1)	Qualitative interviews	Perspectives on acceptability, feasibility, and workflow impact	Content analysis by construct by role, e.g., CP, clinician, administrator	Prior to the start of the enrollment period (− *T*_1_)
CACP effectiveness (aim 2 primary)	EHR review	Days alive out of ED or hospital 0 and *T*_3_	The number of days the patient was alive and out of the ED or hospital (not in hospital, excluding planned hospital admissions for scheduled surgeries, procedures, and/or treatments) between 0 and *T*_3_	Comparison between the groups will be made at *T*_3_
CACP effectiveness (aim 2 secondary)	EHR review	Unplanned ED visits, hospitalizations, or death (composite endpoint and individual)	The number of events per participant per 30 days, the percent of participants with events within 30 days, and time to event(s). Will report as a composite outcome and individually	Comparison between the groups at *T*_4_ and *T*_5_
CACP effectiveness (aim 2 exploratory)	EHR review	SNF care	The percent of participants admitted to SNF within 30 days of randomization and duration of SNF stay	Comparison between the groups will be made at *T*_3_
CACP safety (aim 2 secondary)	EHR review	Unplanned hospitalizations, ED visits, falls with injury, medication errors with harm, and death	The percentage of patients with events within 30 days, the total number of events within 30 days, and time to event(s). Will report as a composite outcome and each outcome individually	Comparison between the groups at *T*_3_ and the day after randomization to *T*_3_

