Aim 2 will evaluate CACP effectiveness (compared to usual care) and implementation outcomes using mixed methods. The primary effectiveness outcome is the number of days alive out of ED or hospital within 30 days of the day following randomization, ascertained by EHR review; this outcome includes all unplanned hospitalizations, ED visits, and deaths, which will also be assessed separately as safety endpoints. This primary outcome measure was selected for its relevance to the desired goal of the CACP program, i.e., shortening and/or preventing ED and hospital utilization. It captures both the initial impact of CP services availability and the effectiveness of the program in meeting the needs of the patient and preventing the return to the ED/hospital subsequent to initial discharge. Planned hospital stays will be excluded from the primary outcome. The secondary outcomes include the proportions of patients experiencing the components of the primary outcome (i.e., percent of patients with unplanned hospitalizations, ED visits, and death), the rates of each component of the primary outcome, the proportion of patients requiring SNF care, as well as patient-reported health-related quality of life (HRQoL) and treatment burden using the patient-reported EQ-5D [19] and PETS [20] measures. For patients in the CACP program, patient satisfaction will also be evaluated. Implementation outcomes, organized by the RE-AIM implementation evaluation framework (Reach, Effectiveness, Adoption, Implementation, and Maintenance), as shown in Table 2, will be ascertained using administrative and EHR data and interviews. Reach and adoption outcomes include metrics for the eligible population, while other implementation outcomes are specific to the intervention group. Additional secondary analyses will assess for the heterogeneity of treatment effects as a function of baseline ED/hospital utilization, source of referral, reason for referral, services delivered, patient demographics (age, sex, rurality, race/ethnicity, limited English proficiency, area-level deprivation), number of CP visits, and duration of CP care. Sensitivity analyses will be performed excluding hospice deaths and utilizing the per-protocol rather than the intention-to-treat approach.

Aim 3 will assess acceptability/satisfaction and perceived sustainability using surveys [21] and interviews with patients, CPs, clinicians and other members of the health care team, and administrators.

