## Statistical methods

### Statistical methods for primary and secondary outcomes {20a}

#### Aim 1

We will use methods of rapid qualitative analysis, guided by constructs in the Consolidated Framework for Implementation Research (CFIR) [22]. Members of the study team will meet to review notes and audio recordings from interviews and discuss issues that may impact implementation, including those that should be addressed before trial enrollment commences. Notes will be summarized in a template guided by the CFIR framework and imported into qualitative software (NVivo, QSR International) for data management. Summaries will be presented at biweekly study team meetings for discussion of potential actions, including changes to the implementation plan.

#### Aim 2

The main analysis of the primary outcome will be based on the intention-to-treat (ITT) principle, with all patients randomized to CACP compared to all patients randomized to usual care. The ITT sample will comprise all patients who were randomized and completed the baseline assessment. The primary outcome (CACP effectiveness) is defined as the number of days the patient was alive and outside of the ED or hospital (excluding planned hospital admissions for scheduled surgeries, procedures, and/or treatments). Outcomes will also be analyzed in the per-protocol subset. The per-protocol sample will comprise all patients in the ITT arm except for those who did not follow protocol, i.e., patients who did not receive CP services in the intervention arm.

The mean number of days out of the ED or hospital for the intervention group will be compared to that of the control arm. Statistical significance, and a two-sided confidence interval for the difference between arms, will be assessed by using the two-sample *t* test. The distributional assumptions for the test will be assessed by calculating the skew and kurtosis for the bootstrap distribution of the sample difference between means. The Hodges-Lehman shift estimator for the Wilcoxon rank-sum test will be used if the absolute value of the skew or kurtosis-minus-three are greater than 1.5.

Other continuous outcome measures will be assessed by the same method as the primary outcome measure. Categorical measures will be assessed by using the Pearson chi-square test, or the Fisher exact test will be used if the minimum expected cell count is less than five.

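### Table 1 compares duration of SNF stay between arms, a quantity that in its ordinary sense exists only for patients admitted to a SNF after randomization; SNF days per randomized patient should be compared instead

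*Protocol article*

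**What the plan says.** In Table 1 (Outcomes {12}) the SNF row is labelled "CACP effectiveness (aim 2 exploratory"). Its aggregation column reads "The percent of participants admitted to SNF within 30 days of randomization and duration of SNF stay", and its time-point column reads "Comparison between the groups will be made at *T*_3", which the table notes define as 30 days after allocation. The text of the same section mentions only "the proportion of patients requiring SNF care" and does not mention duration.

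The methods come from Statistical methods {20a}. For the percent admitted: "Categorical measures will be assessed by using the Pearson chi-square test", with the Fisher exact test for small expected counts. For duration: "Other continuous outcome measures will be assessed by the same method as the primary outcome measure". That method is a two-sample t test, or the Hodges-Lehmann and Wilcoxon approach if the skew or kurtosis check fails.

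Two further places bear on who enters a SNF. Eligibility {10} excludes patients if "they are requesting services in a location outside the CACP service area or in a skilled nursing facility (SNF"). Intervention description {11a} expects some usual-care patients to have "alternative care pathways (e.g., home health agency, SNF, frequent clinic visits) to meet their clinical needs".

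**The concern.** A stay has a length only if it took place. Patients seeking services in a SNF are excluded at entry, so the stays that count arise after randomization. The protocol itself names SNF as one way in which usual care may meet needs that the program would meet at home. Allocation can therefore change which patients are admitted. If it does, those admitted in the two arms are different kinds of patient, and a t test or rank test of their stay lengths mixes the program's effect with that selection.

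The natural worry is that the program keeps the milder SNF candidates at home. The stays that remain are then the longer ones, and mean stay rises although total SNF use falls. The metric matters beyond its rank because the primary outcome, as worded, subtracts ED and hospital days but not SNF days. SNF use is where a reader would look to see whether hospital days were replaced by days in another facility.

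**Working it through.** **Inputs.** The protocol gives no SNF admission rate and no stay length, so it has no figure to reproduce. All rates below are assumptions chosen to show the range. The only figure taken from the protocol is the planned 120 patients per group (Sample size {14}).

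**Set-up.** In usual care, a share s of patients has a short SNF stay of 8 days and a share l has a long stay of 20 days, all within the 30-day window. The program averts a fraction a of the short stays and shortens every remaining stay by r days.

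- Usual care: admitted share = s + l; SNF days per randomized patient = 8s + 20l.
- Program: admitted share = s(1 - a) + l; SNF days per randomized patient = s(1 - a)(8 - r) + l(20 - r).
- Mean stay among admitted = SNF days per randomized patient / admitted share.

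**Cases 1 to 4** use s = 0.10 and l = 0.05. Usual care then has 15% admitted, 0.10×8 + 0.05×20 = 1.80 days per randomized patient, and a mean stay of 1.80/0.15 = 12.0 days.

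1. a = 0, r = 2: days 0.10×6 + 0.05×18 = 1.50; mean stay 1.50/0.15 = 10.0.
2. a = 0.5, r = 2: days 0.05×6 + 0.05×18 = 1.20; mean stay 1.20/0.10 = 12.0.
3. a = 0.5, r = 0: days 0.05×8 + 0.05×20 = 1.40; mean stay 1.40/0.10 = 14.0.
4. a = 0.8, r = 0: days 0.02×8 + 0.05×20 = 1.16; mean stay 1.16/0.07 = 16.6.

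**Case 5** is a deliberate extreme: s = l = 0.10, all short stays averted, no other change. Usual care: days 0.10×8 + 0.10×20 = 2.80; mean stay 2.80/0.20 = 14.0. Program: days 0.10×20 = 2.00; mean stay 2.00/0.10 = 20.0.

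| Case | Percent admitted, usual care vs program | Difference in mean stay among admitted (days) | Difference in SNF days per randomized patient |
|---|---|---|---|
| 1 | 15 vs 15 | -2.0 | -0.30 |
| 2 | 15 vs 10 | 0.0 | -0.60 |
| 3 | 15 vs 10 | +2.0 | -0.40 |
| 4 | 15 vs 7 | +4.6 | -0.64 |
| 5 | 20 vs 10 | +6.0 | -0.80 |

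The fall in the last column is built in, because the program is assumed only to avert or shorten stays. What the table shows is that the admitted-only difference can then be negative, zero or positive. In case 2 it hides a benefit; in cases 3 to 5 it points the other way. The two measures agree in sign only in case 1, where admission is unchanged. In case 3 the stay-length comparison would rest on about 120×0.15 = 18 and 120×0.10 = 12 patients.

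**The case against.** The strongest reply is that the protocol never says duration is taken among admitted patients only. Days per participant with zeros is an open reading, the sign reversal vanishes under it, and a full protocol or analysis plan not shown here may fix the denominator. This stands in part: the admitted-only denominator is an inference. It is the ordinary sense of the words, though, and the effectiveness row just above in Table 1 states a per-participant count where one is meant.

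A reader might also infer that SNF use as a whole is compared through duration, so that the plan would simply report harm. The documents do not support this. The same row first compares the percent admitted over all participants. In cases 2 to 5 that percentage falls and would be reported beside the longer or unchanged stays, so the selection would be visible.

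A reader might infer further that SNF days after day 30 are counted. The SNF row does not state a cut, but that is silence. The comparison is set at 30 days, Provisions for post-trial care {30} ends outcome ascertainment at day 30, and the EHR is queried at 30 days ({18a}).

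The +6 days needs every short stay averted and no long one, so it marks the end of the range and is not an expectation. Finally, counting zeros does not by itself settle death or readmission: a patient who dies early or returns to hospital accrues few SNF days. That objection is right, and the fix has to meet it.

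**Conclusion.** The point holds for the duration metric only. Read in its ordinary sense, the planned comparison of SNF stay length conditions on a post-randomization event that the intervention may change, and neither the t test nor the rank-based alternative cures that. Under the assumed rates the admitted-only difference runs from -2 to +6 days while SNF days per randomized patient fall by 0.3 to 0.8. With no SNF rates in the protocol, the actual size is unknown, and the problem disappears if duration is counted over all randomized patients with zeros.

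Severity is minor. The metric is the second one in a row that Table 1 labels exploratory. The percent admitted is sound, and the primary outcome, sample size and main conclusion are not touched.

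**What to change.** In the SNF row of Table 1, keep the percent admitted and replace the compared duration with SNF days from the day after randomization through day 30 per randomized patient, zero if never admitted. Report it beside deaths and hospital days in the same window, so that few SNF days because of death or readmission are not read as benefit. Give length of stay among admitted patients by arm descriptively, without a between-arm test.

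One detail of {20a} needs care: the new metric should be reported as a difference in means with its confidence interval. Most patients will have zero SNF days. In case 3, for example, 0.85×0.90 = 0.765 of all between-arm pairs are zero against zero, so the Hodges-Lehmann shift would be zero whatever the true difference in mean days.

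The cost is one table cell and a sentence in the analysis text. It uses the same EHR data and needs no change to sample size or follow-up.

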The EHR will be queried at 30 days, 6 months, and 12 months for ED visits, hospitalizations (excluding planned hospital admissions for scheduled surgeries, procedures, and/or treatments), and other outcomes of interest not collected directly from the patient. The study setting includes two hospital systems with the same Epic EHR and the ability to view records regardless of event location; therefore, we anticipate high completeness of EHR data for this trial. However, we will supplement these data as needed with patient-reported information about ED visits and hospitalizations, ascertained in the 30-day survey and confirmed with phone follow-up.

We will also survey clinicians and other members of the health care team who referred participants enrolled in the CACP intervention arm, administrators involved with the CACP program, and community paramedics and interview purposive samples of clinicians, administrators, and community paramedics. These surveys will be completed using a web-based survey platform. Survey invitations will be sent by email, and non-responders will receive up to three reminder contacts. Interviews will be conducted in-person or by telephone or video conference, and audio recorded and transcribed for analysis.

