### Methods in analysis to handle protocol non-adherence and any statistical methods to handle missing data {20c}

Primary analyses will be conducted using an intention-to-treat approach. Secondary analysis will be conducted using the per-protocol approach, where patients randomized to the CACP arm who never received the intervention or did not complete the intervention (i.e., did not respond to CP service calls to be scheduled and had to be administratively discharged from the CACP program) will be excluded. Patients randomized to the control condition will not be eligible to receive CP services during the 30-day follow-up period. We will confirm this using an EHR review and exclude any patients who received CP care during that period.

Missing data: For the primary outcome, missing data (e.g., loss to follow-up, withdrawal, death) are expected to be minimal at 30 days, as data are collected from the EHR and are part of the standard of care. Primary analyses will be conducted on the intention-to-treat population. For missingness greater than 20%, multiple imputation will be used.

If patients self-report on *T*_3_ surveys any hospitalizations or ED visits not captured in the EHR, the study staff will confirm those visits using phone follow-up. We will report the percentage of missing data for all primary and secondary outcomes at each time point, as well as for individual survey items. For validated measures with multiple items, we will follow scoring guidance for missing data.

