#### Adverse event reporting and harms {22}

The study team will monitor for AE in both groups including ED visits, unplanned hospitalizations, deaths, falls with injury, and medication errors. SAEs for this study are any events that result in death, are life-threatening or place the participant at immediate risk of death from the event as it occurred, result in an ED visit or hospitalization, or cause persistent or significant disability or incapacity. The study statistician will check for hospitalizations, ED visits, and deaths on a weekly basis. Additionally, study coordinators review patient charts over the course of the study volunteer period, ensuring all adverse events are properly reported to the IRB as required per protocol. AEs and SAEs will be tracked in an Excel adverse event tracking log by the study research coordinators. AE and SAE that occur will be reviewed by the adjudication committee, which is comprised of clinical experts in hospital medicine, emergency medicine, cardiology, primary care, and paramedicine. The principal investigator is not a member of the adjudication committee.

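### Falls with injury and medication errors with harm may be detected unequally between arms: they rest on chart review, and the patient-report back-up used in both arms leaves them out

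*Protocol article*

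**What the plan says.** All references are to the protocol article.

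- **Outcomes {12}, Table 1, CACP safety row.** The endpoints are "Unplanned hospitalizations, ED visits, falls with injury, medication errors with harm, and death". The measurement is EHR review. Percentages, counts and times to event within 30 days are compared between arms: "Will report as a composite outcome and each outcome individually".
- **Plans for assessment and collection of outcomes {18a}.** The EHR is queried for ED visits, hospitalizations and "other outcomes of interest not collected directly from the patient". For two event types there is a second source: "we will supplement these data as needed with patient-reported information about ED visits and hospitalizations", obtained in the 30-day survey and confirmed by phone. The same section says that usual-care participants have no access to CP services.
- **Missing-data section {20c}.** The back-up has the same scope here: "any hospitalizations or ED visits not captured in the EHR, the study staff will confirm those visits using phone follow-up".
- **Adverse event reporting and harms {22}.** "The study statistician will check for hospitalizations, ED visits, and deaths on a weekly basis". The other adverse events are left to chart review: "study coordinators review patient charts over the course of the study volunteer period".
- **Intervention description {11a}.** "Visits are limited to up to two per day". CPs usually report after every visit, by EHR message, EHR chat or telephone. Most usual-care patients are expected to be sent to the ED and admitted, or to have other pathways such as home health, a skilled nursing facility or frequent clinic visits.
- **Who will be blinded {17a}.** The article accepts that CP notes may appear in the chart, but only as a limit on blinding the adjudicators.

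**The concern.** The intervention adds to the record from which these two outcomes are read, and it does so in one arm only. A visiting paramedic may note a fall or a medication error that would otherwise never reach a chart. In usual care, the same event is recorded if an inpatient nurse, a home health nurse or a clinic happens to see it, or if the patient seeks care. What is counted then depends partly on who was looking, and that differs by arm and probably by referral source.

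Hospitalization, ED visit and death are much less exposed, because they generate a record wherever they occur, and the first two also have the patient-report back-up. Falls with injury and medication errors with harm are the only components of the safety row that are not also effectiveness events, so they add specific information about moving care into the home. If their detection differs between arms, the comparison cannot be read as a comparison of harm alone. A larger sample would not remove this bias. Adjudication does not repair it either, because the committee grades relatedness and severity of events that have already been found.

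**Working it through.** The plan gives no figure for this point, so there is none to reproduce. The check has two parts.

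**1. Sources described, by event type**

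| Event | EHR / chart review | Statistician's weekly check | 30-day patient report with phone confirmation, both arms |
|---|---|---|---|
| ED visit | yes | yes | yes |
| Hospitalization | yes | yes | yes |
| Death | yes | yes | not applicable |
| Fall with injury | yes | no | not described |
| Medication error with harm | yes | no | not described |

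The last two rows have no described source that works the same way in both arms.

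**2. Illustration of size**

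Inputs:
- True 30-day risk p: assumed equal in both arms. The documents give no value; 5% is used below.
- Detection probabilities s_C (CACP) and s_U (usual care): assumed, between 50% and 90%. The documents give none.
- Patients per arm: 120, from Sample size {14}.

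Formulas: observed risk = p × s. Observed risk ratio = (p × s_C) / (p × s_U) = s_C / s_U, so the assumed true risk cancels.

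| s_C | s_U | Observed risks at p = 5% | Expected events per 120 | Observed risk ratio |
|---|---|---|---|---|
| 90% | 90% | 4.5% vs 4.5% | 5.4 vs 5.4 | 1.00 |
| 90% | 70% | 4.5% vs 3.5% | 5.4 vs 4.2 | 1.29 |
| 90% | 50% | 4.5% vs 2.5% | 5.4 vs 3.0 | 1.80 |
| 50% | 90% | 2.5% vs 4.5% | 3.0 vs 5.4 | 0.56 |

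The third row would show a false excess in the CACP arm and the fourth a false benefit.

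The s values are averages over all events. If a share f of events leads to ED or hospital care and is detected with the same probability h in both arms, then s = f × h + (1 − f) × m, where m is the arm's detection of the remaining events. Only m differs between arms, so the larger f is, the closer the ratio comes to 1.

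**Chance of a significant false CACP excess** (p = 5%, 90% vs 50%, 120 per arm, two-sided 0.05). Summing the two binomial distributions under the planned rule (Pearson chi-square, or Fisher exact when the smallest expected count is below 5) gives about 8%. Fisher exact throughout gives about 6%, and a normal approximation gives about 13%. The damage is therefore mainly a biased estimate, not a frequent false significant result.

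**The case against.** The other side has several good arguments.

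- **Chart review may not be the only source.** In Table 3 the row for falls and medication errors carries no EHR tag, while the row above it does, and the footnote lists surveys and interviews among the assessments. The article condenses a fuller protocol and does not print the survey items. This stands in part: the article cannot show that no such item exists. But Table 1 does name EHR review for this row, and both statements of the patient-report back-up limit it to ED visits and hospitalizations.
- **Usual care is also observed.** Admission, home health, skilled nursing and clinic visits are expected. This stands, and it is why the direction is open. It does not make the sources equal.
- **CP contact is limited.** Two visits a day is a ceiling, patients graduate when the referral goals are met, and the planned duration bands start below 10 days. This stands and reduces the likely size.
- **The endpoints require injury or harm.** Such events often lead to care that is visible in the shared EHR. This stands and confines the problem mainly to events without ED or hospital care.
- **Reliance on routine records is an ordinary pragmatic choice.** That is true, but the plan already supplements those records in both arms for two event types.

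A reader might go further and infer that usual-care patients at home have no observer, or that CACP will appear to cause falls and errors it merely recorded. The documents do not support either inference: they name other observers in usual care, and better recording there could equally produce a false CACP benefit.

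A reader might also want the main comparison restricted to survey reports and chart entries not made by CPs. That would not be symmetric. It drops CP notes, keeps home health and inpatient notes, and removes harms that paramedics actually saw.

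**Conclusion.** The point holds in a limited form. For falls with injury and medication errors with harm, the article describes chart review as the source, adds home observers and EHR entries in one arm only, and leaves both events out of the patient-report back-up offered to both arms. Unequal detection is a reasonable inference from this design, not something that the documents demonstrate. Its direction and size are not settled.

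The risk ratios of 1.29, 1.80 and 0.56 rest entirely on assumed detection rates and equal true risk. They show what unequal detection would do, not what to expect. The primary outcome is not affected. The rule for pausing accrual is affected only slightly, because a fall or medication error counts as a serious event mainly when it leads to ED or hospital care, death or disability. This is a cheap improvement, not a flaw that undermines the trial.

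**What to change.** 1. Add two dated items to the existing 30-day survey in both arms, for participants not yet surveyed: any fall with injury, and any medication error with harm, within the 30-day window. Confirm positive answers by the phone follow-up already planned for ED visits and hospitalizations.
2. Add a field to the adverse event log that records every source of each event: CP note, inpatient, skilled nursing, home health, clinic or ED record, survey.
3. Keep the all-source comparison, including events from CP notes, as the main safety analysis.
4. Add a sensitivity comparison restricted to survey-reported events, the source common to both arms. Add a table of events by source and arm that separates those known only from CP notes from those known only from inpatient, skilled nursing or home health notes.

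**Cost.** Two survey items, one log field and a short addition to the analysis wording, with no new visit or assessor. The drawbacks are a slightly longer survey, recall by unblinded participants (contact attempts may run to day 90), non-response, and incomplete coverage: recruitment began in January 2022, so some participants are already past day 30. The source field can be completed for everyone from the charts.
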